#### Weaning process

To standardise the weaning process across all study sites, physicians are required to assess daily whether patients meet the criteria for an SBT. The criteria align with the weaning protocol developed by the Dutch Society of Intensive Care,^13^ which is supported by recent literature.^14^,^16^ We strongly encourage physicians to adhere to the criteria outlined below.

Criteria for initiating an SBT:

Adequate oxygenation: oxygen saturation (SpO_2_) >90% with fraction of inspired oxygen (FiO_2_) ≤50% and positive end expiratory pressure (PEEP) ≤8 cmH_2_O.Adequate respiratory rate: respiratory rate ≤34/min.Stable cardiovascular status: systolic blood pressure 90–160 mm Hg without or with minimal vasopressor use, heart rate ≤140/min.

When a patient meets all of the above criteria, an SBT will be performed. This trial should last at least 30 min and can be conducted using one of the following methods:

Using the T-piece.Pressure support mode, with pressure support (PS) ≤8 cmH_2_O and PEEP ≤7 cmH_2_O.Continuous positive airway pressure (CPAP) mode, with PEEP ≤7 cmH_2_O.

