### Intervention description

#### Levosimendan

After randomisation, subjects will receive either levosimendan or a placebo at a starting dose of 0.1 µg/kg/min,^17^,^19^ diluted with glucose 5%. Use of an initial bolus of levosimendan is generally not recommended, mostly to minimise the risk of vasodilation.^20^ In absence of rate limiting effects (heart rate >130/min, hypotension defined as mean arterial blood pressure (MAP) <65 mm Hg, infusion rate is increased after 4 hours to 0.2 µg/kg/min for the remaining 20 hours. If the patient has rate-limiting side effects at the dose of 0.2 µg/kg/min infusion rate is reduced to 0.1 µg/kg/min or less or even discontinued.^6 21^ This dosage will be repeated weekly until successful weaning from invasive ventilator or until the primary endpoint is reached, with a maximum of four doses administered.

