### Criteria for discontinuing or modifying allocated interventions

Study medication (levosimendan or placebo) will be administered intravenously at a starting rate of 0.1 µg/kg/min, with the option to increase to 0.2 µg/kg/min after 4 hours if well tolerated. If a patient develops haemodynamic instability, defined as a heart rate >130 beats/min or hypotension with mean arterial pressure <65 mm Hg, the infusion rate will be reduced to 0.1 µg/kg/min or lower, or discontinued altogether if necessary or if requested by the patient. Any discontinuation of treatment will be documented in the electronic case report form, including the underlying reason.

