### Strategies to improve adherence to interventions

To ensure adherence to the study protocol, each study site will have a dedicated team trained by the steering committee. Training will include an initiation visit, review of standard operating procedures (SOPs), and a clinical lesson for all nurses and physicians involved in the trial. Additionally, the research pharmacy will receive an SOP for proper preparation and blinding of study medications. ICU nurses will also receive an SOP on infusion rates and when to adjust dosages, with close monitoring of both adjustments and side effects.

The weaning process will be standardised as much as possible, with daily assessments by the intensivist to determine whether SBT criteria are met.

Any deviations from the study protocol will be documented in the eCRF and evaluated during data safety monitoring board (DSMB) meetings.

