### Relevant concomitant care permitted or prohibited during the trial

Treating physicians may prescribe any concomitant medications or treatments deemed necessary to provide adequate patient care without restrictions due to this research. Vasopressors, inotropes and antiarrhythmic medications will be considered relevant medications and must be recorded in the eCRF.

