### Outcomes

The primary endpoint of the study is the number of ventilator-free days and alive (VFD) at day 28 from randomisation. This is a composite endpoint combining both mortality and the duration of ventilation. In case of death, the subject will be assigned a value of 0 VFD. Day 0 will be defined as the day of randomisation.

Secondary outcomes include ICU mortality, VFD from randomisation up until day 90, safety endpoints such as hypotension (MAP <65 mm Hg), cardiac dysrhythmia (atrial fibrillation, ventricular arrhythmias), dyspnoea sensation, EQ-5D-5L questionnaire at baseline, 3 months and 12 months, reintubation rate, non-invasive support after detubation and pharmacokinetics of levosimendan up until 5 days.

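### The hypotension safety endpoint counts only MAP <65 mm Hg, so vasodilation that a vasopressor keeps above that threshold is not counted and the harm comparison can be understated

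*Protocol article*

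**What the plan says.** The Outcomes section names "safety endpoints such as hypotension (MAP <65 mm Hg" among the secondary outcomes. Hypotension is thus defined by a pressure threshold alone. No outcome in that section refers to starting, raising or needing a vasopressor.

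Four other places bear on this:

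- The section on concomitant care states: "Treating physicians may prescribe any concomitant medications or treatments deemed necessary to provide adequate patient care without restrictions due to this research". It then adds: "Vasopressors, inotropes and antiarrhythmic medications will be considered relevant medications and must be recorded in the eCRF". Vasopressors are therefore free to use and are recorded, but they are not an outcome.
- The SBT criteria under Weaning process accept "systolic blood pressure 90–160 mm Hg without or with minimal vasopressor use", so some patients may already have a vasopressor running.
- The Levosimendan section advises against an initial bolus, "mostly to minimise the risk of vasodilation", and treats hypotension as one of two rate-limiting effects.
- The section on discontinuing or modifying the intervention uses the same threshold for haemodynamic instability: "defined as a heart rate >130 beats/min or hypotension with mean arterial pressure <65 mm Hg, the infusion rate will be reduced".

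**The concern.** Hypotension is a harm the protocol itself expects, because it is built into the infusion rules. In an ICU a falling pressure is usually seen and often treated. If a vasopressor is started or turned up while MAP is still at or above 65 mm Hg, the patient has had the effect and needed treatment for it, but the stated endpoint records nothing. This happens even if the plan is followed exactly.

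Blinding does not close the gap. Clinicians respond to the pressure they see, so if levosimendan lowers pressure more often, pre-emptive support would plausibly be more frequent in that arm. At stake is the safety comparison, both in the final report and in what the DSMB sees if its review of hypotension rests on this endpoint.

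**Working it through.** **The plan's own figure.** The documents give no event rate, effect or power for hypotension, so there is nothing to reproduce for this endpoint. The only input taken from the plan is 125 patients per arm (Sample size section). All event rates and masked shares below are assumptions.

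**What is and is not counted.**

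| Course of events | MAP <65 reached? | Counted? |
|---|---|---|
| MAP falls below 65, vasopressor then started | yes | yes |
| MAP falls below 65, infusion then reduced under the protocol rule | yes | yes |
| MAP drifts down, vasopressor started or raised, MAP stays at or above 65 | no | no |

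Only the third row is lost.

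**Effect of losing it.** Let p be the true rate of vasodilatory events (MAP <65, or a vasopressor given to prevent it) and m the share pre-empted. The observed rate is p × (1 − m). Power is for a two-sided 0.05 comparison of two proportions (normal approximation), n = 125 per arm:

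power = Φ[(d − 1.96 × SE0) / SE1], where d is the difference in rates, SE0 = √(2 p̄(1 − p̄)/125), p̄ is the mean of the two rates, and SE1 = √(p1(1 − p1)/125 + p0(1 − p0)/125).

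Assumed true rates: 30% levosimendan, 15% placebo.

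| Masked, levosimendan / placebo | Observed rates | Risk difference (points) | Risk ratio | Power |
|---|---|---|---|---|
| 0 / 0 | 30% / 15% | 15 | 2.0 | 81% |
| 30% / 30% | 21% / 10.5% | 10.5 | 2.0 | 63% |
| 50% / 50% | 15% / 7.5% | 7.5 | 2.0 | 47% |
| 70% / 70% | 9% / 4.5% | 4.5 | 2.0 | 29% |
| 50% / 30% | 15% / 10.5% | 4.5 | 1.43 | 19% |

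Example for the last row: 0.30 × 0.50 = 0.15; 0.15 × 0.70 = 0.105; 0.15 / 0.105 = 1.43.

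At higher assumed rates (45% against 30%) the pattern is the same. With no masking the ratio is 1.50 and power 69%. Equal masking of 50% keeps the ratio at 1.50 with power 33%. Masking of 50% on levosimendan and 30% on placebo gives 22.5% against 21%, a ratio of 1.07 and power of 5%.

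Equal masking multiplies both rates by the same factor, so the ratio cannot move; only the risk difference and the power fall. The ratio moves toward 1 when masking is heavier on levosimendan. If masking were heavier on placebo, the ratio would rise: at 45% against 30%, masking 30% on levosimendan and 50% on placebo gives 31.5% / 15% = 2.10.

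**Cost of a composite.** Suppose a share b of patients in each arm has a vasopressor increase for unrelated reasons, independent of the drug effect. The composite rate is 1 − (1 − p)(1 − b). Starting from 30% against 15% with no masking:

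| b | Composite rates | Risk ratio | Power |
|---|---|---|---|
| 10% | 37% / 23.5% | 1.57 | 64% |
| 20% | 44% / 32% | 1.38 | 50% |
| 30% | 51% / 40.5% | 1.26 | 38% |

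So a composite that replaced MAP <65 would have a dilution problem of its own.

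**The case against.** The strongest reply is that MAP <65 mm Hg is a conventional threshold, nothing in the documents contradicts it, and much of the supposed gap is covered. The infusion rule acts at the same threshold, so action under it follows a countable event. Vasopressors are recorded, nurses follow an SOP "with close monitoring of both adjustments and side effects", and adverse events in the intervention period are documented. The safety list is introduced as examples, and a full SAP is announced that may report vasopressor use by arm. The Discussion also cites earlier trials with less vasopressor need on levosimendan, which runs against the assumption of more pressor use in the active arm. Finally, no powered test of hypotension is stated, so power is only a yardstick.

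Much of this stands. It limits the size and certainty of the concern, and the dilution arithmetic rules out simply replacing the endpoint. It does not remove the gap: the wording opens the list of endpoints, not the definition in brackets, and recording a drug is not the same as counting it as an outcome.

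A reader might infer more: that all clinician-treated vasodilation goes uncounted, or that the comparison is biased toward no difference as a matter of fact. The documents support neither. Treatment begun after MAP has dropped below 65 follows a counted event, and nothing shows how often pre-emption occurs or that it differs between arms.

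**Conclusion.** The concern holds in a limited form. The stated definition misses vasodilation that a vasopressor pre-empts, so it can understate the absolute difference in an expected harm. It can bias the risk ratio toward 1 if pre-emption is more frequent on levosimendan, which is plausible but not shown.

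The size cannot be derived from the documents. Over the equal masking shares assumed above (30% to 70%), the risk difference falls in proportion, from 15 points to between 10.5 and 4.5, with the ratio unchanged. Only the unequal case (50% against 30%) lowers the ratio, from 2.0 to 1.43.

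Nor do the documents show that the DSMB would be misled: the oversight section gives it a general safety remit and does not confine it to this endpoint. This is a worthwhile and inexpensive improvement to a secondary safety comparison. It does not touch the primary endpoint or the sample size.

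**What to change.** Keep MAP <65 mm Hg as the hypotension endpoint. Add a second named safety endpoint: a new start of, or an increase in, vasopressor, over the same prespecified window around each infusion in both arms. Report by arm MAP <65, vasopressor start or increase, and the composite of the two. Show the components separately, because unrelated vasopressor changes add noise and dilute the composite ratio.

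Before fixing the definition, confirm what the eCRF holds. The protocol requires vasopressors to be recorded but does not say that timing and dose are captured. If dose changes cannot be placed in the window, use new starts only and state that increases in patients already on a vasopressor are then missed.

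The cost is a derived variable and a few table rows, plus possibly a timing or dose field in the eCRF. The DSMB first meets after 25 inclusions, so an early decision would let its reports show both components. No dose, infusion rule or clinical decision changes.

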### Participant timeline

The time points for enrollment, interventions and follow-up can be found in table 1.

**Table 1 T1:** Participant timeline

	Pretreatment						Follow-up
	Day −1	Day 0	Day 1	Day 2, 3, 4, 6	Day 8, 15, 22	Day 28	Day 90, 365
Enrolment							
Eligibility screening	X						
Baseline characteristics		X					
Informed consent*		X					
Randomisation		X					
Interventions							
EQ-5D-5L		X					X
Study medication†			X		X		
Baseline lab‡		X					
TDM levosimendan				X			
Dyspnoea scores			Daily from extubation up until day 28/ICU discharge				
Assessments							
Ventilation data			Daily				
Adverse events/safety endpoints			Daily				
Reintubation rate			Daily from extubation up until day 28/ICU discharge				
Life status, duration of ventilation, ICU and hospital admission						X	X

* Informed consent is obtained before randomisation.

† Patients will receive the study medication weekly until successful weaning or until the primary endpoint is reached, with a maximum of four doses administered.

‡ In baseline lab we will include NTproBNP as a marker of cardiac failure and in case of a female a pregnancy test.

ICU, intensive care unit; NT-proBNP, N-terminal pro b-type natriuretic peptide; TDM, therapeutic drug monitoring.

### Sample size

The mean and SD of ventilator-free days at day 28 (VFD-28) are not precisely known for our target population (patients who are invasively ventilated and have a failed separation attempt). Based on data from the PReVENT dataset,^26^ we estimate the mean VFD-28 to be 15.6 days, with an expected SD of 10.6.

We aim to detect a clinically meaningful improvement of 25% in VFD-28, corresponding to an absolute difference of 3.9 days. A sample size of 117 patients per group provides 80% power to detect this difference using a two-sided alpha level of 0.05. To account for potential non-normality in the distribution of VFD-28, we have increased the sample size to 125 patients per group, resulting in a total sample size of 250 patients.

### Recruitment

With a sample size of 250 patients and an inclusion rate of 10 patients/months we expect that the recruitment period is approximately 2 years after all eight centres start enrolling patients. Eligible patients will be identified from ICUs in participating hospitals where patients are receiving invasive ventilation based on daily screening on the study’s inclusion and exclusion criteria.

### Assignment of interventions: allocation

#### Sequence generation

Clinical research platform Castor Electronic Data Capture (https://www.castoredc.com/) will be used to perform the randomisation and is Good Clinical Practice. Participants will be randomised in a 1:1 allocation ratio to ensure equal distribution between the intervention and control groups. To minimise potential site-specific effects, stratified randomisation by study centre will be applied.

#### Concealment mechanism

Patients will be randomised in Castor after obtaining informed consent. Concealment will be ensured by the use of blocks with randomly permuted sizes.

#### Implementation

The local principal investigator, who is trained by the steering committee, and the dedicated study team on the study site will enrol and randomise patients and make sure they will receive the dedicated strategy. The unblinded team, primarily pharmacy personnel, will receive the randomisation results and ensure that the assigned medication is provided to the nurse for administration to the patient.

### Assignment of interventions: blinding

#### Who will be blinded

This study will follow a double-blind design, meaning that both participants and all investigators involved in recruitment and outcome assessment will remain blinded to treatment assignments at all times.

#### Procedure for unblinding if needed

Emergency unblinding, however, remains possible. This is strictly limited to situations where knowing the patient’s assigned treatment is critical for safety, such as life-treating arrhythmias or severe adverse events. In such cases, the investigator will contact the unblinded team, who will provide the information about the treatment assignment.

### Data collection and management

#### Plans for assessment and collection of outcomes

Most study data will be collected from electronic patient records, ensuring accurate and efficient documentation. Baseline characteristics will be recorded on enrolment, including demographic data, medical history, Acute Physiology And Chronic Health Evaluation II (APACHE II) and Sequential Organ Failure Assessment (SOFA) scores, ECG, medication use, intoxication and baseline laboratory. If a cardiac echocardiogram is performed as part of standard care to evaluate potential weaning failure,^27^ data on ejection fraction and diastolic function will be collected. However, if a cardiac ultrasound is not performed as part of standard care, no additional ultrasound will be conducted for study purposes.

Clinical parameters including ventilator settings, respiratory mechanics, haemodynamic status and laboratory values will be recorded daily until day 28 or ICU discharge. Blood samples will be collected in selected centres to assess the pharmacokinetics of levosimendan in critically ill patients. Baseline NT-proBNP measurements will be used to identify patients with a cardiac origin of weaning failure. Pharmacokinetic assessments will be conducted at 24, 48, 72 and 120 hours after completion of the first dose of the study medication. While blood sampling will be performed in most patients, logistical constraints may prevent its feasibility in all participating hospitals, meaning not all patients will undergo these assessments.

Dyspnoea scores will be assessed using a standardised daily dyspnoea scale. The score will only be evaluated in patients with a Richmond Agitation-Sedation Scale score between −2 and +2, and in the absence of delirium or confusion as determined by the confusion assessment method for the intensive care unit (CAM-ICU) assessment. After confirming adequate mental status using two trigger questions, patients will be asked whether they are experiencing dyspnoea. If they confirm the presence of dyspnoea, a visual analogue scale (VAS) ranging from 0 to 10 will be used to quantify its severity. The EuroQol 5-dimensions 5-level questionnaire is a standardised instrument to describe and value health, consisting of a descriptive system and a VAS. The EQ-5D-5L will be performed at baseline (describing the situation before ICU admission), after 3 months and after 12 months.

Healthcare resource utilisation including reintubation rates, ICU readmission within 90 days, need for non-invasive respiratory support, mortality and ICU length of stay will be retrieved from electronic patient records and documented in the eCRF to perform a Health Technology Assessment analysis.

#### Plans to promote participant retention and complete follow-up

Almost all relevant study data in the WEANLESS study can be extracted from the patient’s medical record, minimising the risk of loss to follow-up for the primary endpoint. Since all participants are admitted to the ICU, missing data is expected to be minimal. To further reduce the risk of loss to follow-up, patients and relatives are informed about the follow-up process, the informed consent procedure and the research team’s contact details are provided on all consent forms.

### Data management

To maintain data integrity, research personnel at each site will be trained in standardised data collection procedures, automated validation checks within the eCRF will flag inconsistencies or missing data for review and data entry will include range checks and automated calculations to minimise errors. All study data will be securely stored and retained for 15 years after study completion, following regulatory guidelines. Blood samples will be processed and stored according to study protocol. No biological specimens will be used for genetic or molecular research, either within this trial or for future studies.

### Confidentiality

Patient data will be pseudonymised using a unique identification code that is not linked to personal identifiers. All personal data handling will comply with the General Data Protection Regulation. Coded study data may be shared between participating hospitals using secure data-sharing platforms designed for clinical research.

### Plans for collection, laboratory evaluation and storage of biological specimens for genetic or molecular analysis in this trial/future use

Blood samples will be collected for analysis of pharmacokinetics and future research. It will be stored for a maximum of 10 years in the Radboudumc. Patients may provide separate consent for the use and storage of the biological specimens.

### Statistical methods

#### Statistical methods for primary and secondary outcomes

For data analysis, an intention-to-treat analysis will be performed on the primary outcome, with patients analysed according to their assigned treatment arms, except for cases lost to follow-up, or patients who are withdrawn due to lack of deferred informed consent. Statistical uncertainty will be expressed by the 95% confidence levels with p value under 0.05 will be considered statistically significant.

The primary analysis of the primary outcome, which is ventilator-free days up until day 28 (VFD-28), will reflect a composite endpoint combining both mortality and the duration of ventilation. This approach integrates the impact of death (assigned a value of 0 VFD) and the length of time a patient remains on invasive ventilation. Day 0 will be defined as the day of randomisation, with the duration of intubation prior to randomisation reported as a baseline variable. The individual components of the composite endpoint, mortality rates and the duration of ventilation, will be described separately for both treatment groups to provide detailed insights into the effects of the intervention. The primary analysis for VFD-28 will use a cumulative logistic regression model to account for the ordinal nature of the endpoint. This model will estimate ORs and 95% CIs to quantify the effect of the treatment compared with the control group.

A pre-planned secondary analysis will be conducted focusing on patients with cardiac failure. This analysis will specifically assess this subgroup to explore potential differential effects of treatment. Patients with cardiac failure will be identified using a baseline NT-proBNP level.

A full statistical analysis plan will be made available before the closing of the database.

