Given the heterogeneity of ICU patients, we prespecified patient characteristics of interest (eg, presence of cardiac dysfunction) that may influence response to levosimendan. While the study is powered to detect an overall effect of the intervention on VFDs, it may lack sufficient power to detect differences within smaller subgroups. Therefore, we will also perform interaction analyses to assess whether the effect of the intervention differs across these prespecified subgroups, providing a more robust and interpretable evaluation of potential effect modification.

In conclusion, the WEANLESS study is designed to provide valuable insights into the role of levosimendan in weaning from invasive ventilation. If found effective in reducing weaning time and improving clinical outcomes, this study could pave the way for the first pharmacological approach to support the weaning process in critically ill patients.

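### Effect modification by cardiac failure is described as a comparison of NT-proBNP-classified subgroups, with interaction tests following from low subgroup power; those tests have less power still, and a continuous NT-proBNP term would use the same data better

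*Protocol article*

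**What the plan says.** All references are to the protocol article.

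- **Statistical methods for primary and secondary outcomes** plans a secondary analysis of patients with cardiac failure, to explore whether the treatment effect differs in them. On who they are it says: "Patients with cardiac failure will be identified using a baseline NT-proBNP level". No cut-off is given. The same section names a cumulative logistic regression for VFD-28 and defers a full SAP.
- **Plans for assessment and collection of outcomes** likewise uses baseline NT-proBNP to pick out patients whose weaning failure has a cardiac origin.
- **Participant timeline**, Table 1 footnote: "In baseline lab we will include NTproBNP as a marker of cardiac failure". The marker is thus part of the planned baseline laboratory work.
- **Discussion** says of the trial: "it may lack sufficient power to detect differences within smaller subgroups. Therefore, we will also perform interaction analyses". It places those interaction analyses across the prespecified subgroups and presents them as the more robust and interpretable way to judge effect modification.
- **Methods for additional analysis** describes the pre-planned cardiac-failure analysis differently, as covering patients in whom cardiac failure was the main reason for intubation.

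**The concern.** Levosimendan is introduced in the article as a cardiac inotrope, while the trial's hypothesis concerns the respiratory muscles. Whether any benefit depends on cardiac failure is therefore central to interpreting the result.

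Three features of the description weaken that analysis.

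1. The modifier is a laboratory value on a continuous scale, but it is described only as a means of sorting patients into groups, and the interaction is placed across groups.
2. The Discussion moves from low subgroup power to interaction tests as though the second answered the first. An interaction test is better than separate subgroup tests because it asks the right question, not because it has more power.
3. The group has two definitions, one from baseline NT-proBNP and one from the reason for intubation. These need not select the same patients.

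At stake is how a null interaction is read. If interaction tests are presented as the answer to low power, a non-significant result invites the conclusion that the effect is the same with and without cardiac failure, which a trial of this size could seldom support.

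**Working it through.** **Inputs from the Sample size section.** "we estimate the mean VFD-28 to be 15.6 days, with an expected SD of 10.6"; "corresponding to an absolute difference of 3.9 days"; "we have increased the sample size to 125 patients per group, resulting in a total sample size of 250 patients". Allocation is 1:1 (Sequence generation).

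**Inputs the article does not give (assumptions).** Cardiac-failure share q, taken as 20-50%. Difference in treatment effect between subgroups, taken first as 3.9 days, the whole design effect, and then varied.

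**Reproducing the plan's figure.** The article states: "A sample size of 117 patients per group provides 80% power to detect this difference using a two-sided alpha level of 0.05". Normal approximation: n = 2 × [(1.960 + 0.842) × 10.6 / 3.9]² = 115.96, so 116 per group. The t-test version gives 116.9, so 117. The stated figure reproduces. At 125 per group, power is 82.9%.

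**Standard errors at 125 per arm, linear model on days.**

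- Main effect: 10.6 × √(2/125) = 1.341 days; z = 3.9/1.341 = 2.909.
- Effect within the subgroup: 1.341/√q, so z = 2.909 × √q for a 3.9-day effect.
- Interaction: 1.341/√(q(1−q)), so z = 2.909 × √(q(1−q)) for a 3.9-day difference.

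The interaction z is the subgroup z times √(1−q), so it is smaller for every share. For effects of equal size the interaction test always has the lower power.

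**Power, two-sided 5%.**

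| Share q | Within subgroup, 3.9 days | Interaction, 3.9 days | Interaction detectable with 80% power |
|---|---|---|---|
| 20% | 25% | 21.4% | 9.4 days |
| 30% | 36% | 26.6% | 8.2 days |
| 40% | 45% | 29.7% | 7.7 days |
| 50% | 54% | 30.7% | 7.5 days |

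The last column is 2.80 × SE(interaction). It is 7.5/3.9 = 1.9 to 9.4/3.9 = 2.4 times the design effect.

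**Dependence on the assumed interaction, shares 20-50%.** 1.95 days: 9-11%. 5.85 days: 41-59%. 7.8 days: 64-83%. At a 10% share, a 3.9-day interaction has 14% power. For 80% power at 3.9 days, total N = 4 × (2.80 × 10.6/3.9)² / (q(1−q)), about 930 (50% share) to 1,450 (20% share), against 250 planned.

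**Continuous marker.** Assume log NT-proBNP is roughly normal and modifies the effect linearly. A cut leaving share q above it separates the group means by D = φ(c)/(q(1−q)) SD, where c is the cut on the standardised scale. The slope that yields a 3.9-day contrast is 3.9/D per SD, and z = slope/1.341.

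| Share q | D | Slope per SD | z | Power, continuous |
|---|---|---|---|---|
| 20% | 1.750 | 2.229 | 1.66 | 38% |
| 30% | 1.656 | 2.356 | 1.76 | 42% |
| 50% | 1.596 | 2.444 | 1.82 | 45% |

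Under this assumption the cut keeps φ(c)²/(q(1−q)) = 0.49, 0.58 and 0.64 of the information.

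**The reverse case.** If the true modification is a step exactly at the cut, the same fractions count against the continuous term. Its z becomes 2.909 × √(q(1−q)) × √0.49 = 0.81 at q = 20% and, with 0.637, 1.16 at q = 50%. Power is then about 13% and 21%, below the 21% and 31% of the cut analysis.

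**Limit of the approximation.** The planned model is ordinal. A small proportional-odds simulation (250 patients, 250 runs, median cut) gave 33% continuous against 24% cut, with a Monte Carlo error of about 3 points. The direction agrees, but the linear figures may be somewhat high.

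**The case against.** **A reader might infer that the continuous value is thrown away.** The article does not say so. It gives no cut-off and no interaction model, and it defers a full SAP, which could use the continuous value. What stands is narrower: every description given is categorical, and the interaction is placed across subgroups.

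**A reader might take 21-31% as the power of the planned test.** It is not a property of the document. It depends on an assumed share and an assumed 3.9-day difference. If the whole 3.9-day overall effect arose in cardiac patients, the difference would be 3.9/q: 7.8 days at 50% and 9.75 days at 40%, with power of about 83% and 95%. This objection is right, and the range must carry its conditions. At smaller shares that scenario soon fails: at 20% it needs 19.5 days, while a mean of 15.6 leaves only 12.4 days below the 28-day ceiling, if cardiac patients start from the same mean.

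**The Discussion may be read too harshly.** It admits limited subgroup power, never claims that interaction tests have adequate power, and replaces separate subgroup tests with the right method. That is fair. Only the inference from one to the other is faulty.

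**The remedy is not a cure.** Power stays below half under favourable assumptions and falls if the modification is a step at the cut. Classification is also a legitimate clinical question. Both points stand, and they are why the categorical analysis should remain as support.

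**Conclusion.** The point holds as a weakness in an exploratory analysis and in the reasoning given for it. It does not touch the primary result.

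- Without any assumption about share: for equal effect sizes an interaction test has less power than the within-subgroup test, so it cannot be the answer to low subgroup power.
- Under a 20-50% share, a 3.9-day difference and a linear approximation: about 21-31% for the interaction, against 25-54% within the subgroup.
- With the interaction size left free: only differences of about 7.5-9.4 days are detectable with 80% power at those shares.
- A continuous term gives about 38-45% if the modification is linear in a roughly normal log NT-proBNP. That is a real gain from data already planned, but power remains low.
- The two definitions of the cardiac-failure analysis conflict on the face of the text, whatever the power.

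**What to change.** 1. Make the main effect-modification analysis a treatment-by-log(NT-proBNP) interaction in the planned cumulative logistic model, fitted in all randomised patients.
2. Show the treatment OR with 95% CI across the NT-proBNP range, for example at the quartiles, with a spline as a check on linearity.
3. Keep the categorical cardiac-failure subgroup as a supportive analysis.
4. Reword the Discussion: present interaction tests as the right comparison, not as the answer to low subgroup power; say that their power is low; and state that a non-significant interaction is not evidence of equal effect. Any power figure should carry its assumed share and interaction size.
5. Reconcile the definition by baseline NT-proBNP (Statistical methods for primary and secondary outcomes) with the definition by reason for intubation (Methods for additional analysis), and say which one the prespecified subgroup means.

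**Cost:** wording in the protocol and the SAP, and one further model on a baseline value already to be measured. The price is an assumption of a smooth relation on the log scale, and a loss of power if the effect changes abruptly at the cut.
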